**Trial Steering Committee (TSC):**

- To provide independent supervision of the scientific and ethical conduct of the trial on behalf of the Trial Sponsor and funding bodies.
- To review data, patient compliance, completion rates, adverse events (during treatment and up to 6 weeks post child-birth).
- To receive and consider any recommendations from the DMEC on protocol modifications.

**Data Monitoring & Ethics Committee (DMEC):**

- To review (initially at approx 3-monthly intervals) overall safety and morbidity data to identify safety issues which may not be apparent on an individual case basis
- To recommend to the TSC whether the trial should continue unchanged, continue with protocol modifications, or stop.

## 8. OUTCOME MEASURES

### 8.1. Primary outcome measure

The primary outcome measure will be the effect of pravastatin on maternal serum sFlt-1 levels individually during the first 72 hours post-randomisation.

### 8.2. Secondary outcome measures

Secondary measures will be:

- The level of maternal circulating sFlt-1 and the ratio of sFlt-1 to PlGF over the first 14 days post-randomisation. Most women are expected to provide regular measurements before childbirth. Pregnancy with pre-eclampsia is expected to last for an average  $11\pm 5$  days, so estimates of effects over the first two weeks are expected to be from a largely complete set of data. All available data, both clinical and biochemical will be examined to see if this influences interpretation of results.
- Severity of pre-eclampsia as indicated by maternal blood pressure, level of proteinuria, platelet count, liver-transaminases, renal function, fetal biometry and umbilical artery blood flow 48 hours after randomisation and for the remainder of the pregnancy.
- Length of gestation post-randomisation, in days.
- Maternal morbidity, as indicated by serum creatinine  $\geq 120\mu\text{mol/L}$ , proteinuria  $\geq 5\text{g/24h}$ ; signs of left ventricular failure (pulmonary oedema, oxygen sats  $< 95\%$ ); hypertension  $\geq 170/110\text{mmHg}$  despite anti-hypertensive treatment; disseminated intravascular coagulation and/or platelets  $< 50 \times 10^9$ ; eclampsia; cerebrovascular event; liver transaminase  $\geq 500\text{IU/L}$ , more than 48 hours after randomisation and for the remainder of the pregnancy.
- Neonatal Apgar score at 1, 5, 10 minutes
- Use of anti-hypertensives
- Level of pravastatin in the cord blood at delivery relative to maternal levels.
- Serious adverse events and reactions

Secondary outcomes will be collected prior to randomisation, daily throughout pregnancy and at birth. The data items collected to identify secondary outcomes are shown in Table 1.

When analyzing secondary outcomes, length of gestation post randomization will be considered the most important indicator of potential clinical efficacy.

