## **7.2. Reporting AEs**

All adverse events, from the first administration of trial treatment until 6 weeks after child-birth, whether observed directly or reported by the patient, will be collected and recorded. Non-serious adverse reactions or events are not required to be reported in an expedited manner, but will be recorded on the daily data collection forms.

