| Liver transaminase                                                | X                      | X                           | X              | X                          | X                           |
| Total cholesterol                                                 | X                      | X                           | X              | X                          |                             |
| C-reactive protein                                                | X                      | X                           | X              | X                          |                             |
| Haematological Measures                                           |                        |                             |                |                            |                             |
| Heamoglobin                                                       | X                      | X                           | X              |                            |                             |
| Platelet count                                                    | X                      | X                           | X              | X                          | X                           |
| WCC                                                               | X                      | X                           | X              |                            |                             |
| Biomarkers                                                        |                        |                             |                |                            |                             |
| Plasma sFlt/ sEng/ PIGF                                           | X                      | X                           | X              | X                          | X                           |
| Anti-hypertensive/ other pre-eclampsia treatment                  | X                      | X                           | X              | X                          |                             |
| Maternal mortality/ morbidity                                     |                        | X                           | X              | X                          | X                           |
| Fetal & Neonatal Measures                                         |                        |                             |                |                            |                             |

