## **9.2. Statistical Analysis**

The primary outcome measure of sFlt-1 during the first three days will be analysed using a repeated measures analysis in SAS PROC MIXED, including the baseline value as a covariate. For the primary analysis the treatment effect will be considered constant over time, secondary analyses will examine the possibility of a trend over time. Plots of mean score over time will be shown for clarification.

As a secondary analysis sFlt-1 and the sFlt-1/PIGF ratio over, initially, the first 14 days and latterly all available data will be analysed using a repeated measures analysis in SAS PROC MIXED. Parameters allowing for treatment arm, time and baseline value will be included in the model. Initially, the treatment effect will be assumed to be constant over time, but if time by treatment interaction is shown to be important by including this parameter in the model (the conventional level of  $p = 0.05$  will be used here) then further investigation into effects at differing time points will be made by analysing the least-square means as above. Plots of mean score over time will be shown for clarification.

The length of gestation (to delivery) post randomisation will be analysed using a Cox Proportional Hazards model. Hazard ratios will be calculated. Kaplan-Meier plots will be produced.

All other continuous measures (clinical measures, etc) will be considered in the same manner as above (adjusting by baseline value if available). Dichotomous outcomes (mortality, etc) will be presented as risk ratios, with a corresponding chi-squared test performed. The latter will be analysed using SAS PROC GENMOD.

Apart from baseline value, no adjustments for covariates will be made in the first instance in any of the investigations above as good balance is expected between groups due to the minimisation procedure at randomisation.

All analysis will be by intention-to-treat, whereby patients will be analysed according to the arm they were randomised to regardless of whether they complied with the treatment. All tests are 2-sided and results will be presented as a point estimate along with 95% confidence intervals. All analyses will be conducted by the trial statistician at the BCTU. A comprehensive Statistical Analysis Plan will be drawn up prior to any analysis and will provide further details on the proposed analysis.

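### The maternal morbidity outcome stops at delivery, which leaves out post-partum events that Table 1 collects and ties the counting window to the length of pregnancy

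*Combined protocol and SAP*

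**What the plan says.** Section 8.2 lists the events that make up maternal morbidity (raised creatinine, heavy proteinuria, left ventricular failure, severe hypertension despite treatment, DIC or low platelets, eclampsia, cerebrovascular event, raised transaminases) and limits them to those arising "more than 48 hours after randomisation and for the remainder of the pregnancy". The severity outcome in the same section carries a near-identical limit, "48 hours after randomisation and for the remainder of the pregnancy". No reason is given for the lag or for stopping at delivery.

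The statements on data collection do not agree with each other:
- The text of 8.2 says: "Secondary outcomes will be collected prior to randomisation, daily throughout pregnancy and at birth".
- Table 1 has a row for "Maternal mortality/ morbidity" marked during pregnancy (with no 48-hour lag), at child-birth, until discharge and at 6 weeks.
- Section 8.3 says that post-partum forms at 6 weeks will gather secondary outcome measurements.
- Section 7.2 collects "All adverse events, from the first administration of trial treatment until 6 weeks after child-birth".

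On analysis, section 9.2 states: "Dichotomous outcomes (mortality, etc) will be presented as risk ratios, with a corresponding chi-squared test performed". It makes no allowance for time at risk. Section 8.2 also says that "length of gestation post randomization will be considered the most important indicator of potential clinical efficacy".

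**The concern.** There are two problems with one cause, the end of the window.

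First, the protocol itself treats the time just after birth as a period of risk. Section 2.1.1 says that eclampsia can appear shortly after pregnancy, and section 6.3.3 places seizure prevention partly in the immediate post-partum period. A post-partum seizure would be recorded under Table 1 and then not counted in the morbidity outcome.

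Second, the window closes at delivery. Time to delivery is the leading secondary efficacy indicator, and section 2.3.4 hopes that the drug will prolong pregnancy. If it does, women on pravastatin are watched for longer than women on placebo, and a risk ratio that ignores time at risk mixes the rate of events with the length of observation. A drug that works could look harmful, or a real reduction in morbidity could be hidden. Objective 2 in section 2.5 asks about effects on the mother, and section 2.6 intends the clinical estimates to inform a larger trial.

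**Working it through.** The plan states no event rate, power or sample size for maternal morbidity, so there is no plan figure to reproduce here. The sample size in section 9.1 concerns sFlt-1 only.

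**Inputs from the documents**
- Time from randomisation to delivery, section 8.2: "Pregnancy with pre-eclampsia is expected to last for an average" 11 days, with a spread of 5 (taken as an SD).
- Window: from day 2 to delivery (8.2).
- Follow-up: to 6 weeks, or 42 days, after birth (Table 1).
- Size: up to 64 women, 1:1, so at most 32 per arm (9.1, 5.3).

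**Inputs assumed**
- A 3-day prolongation (the documents give no size), control risk of 10–40%, and a constant daily hazard that is the same in both arms.

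**Coverage of the window (calendar time, not share of events)**
- Mean window on placebo: 11 − 2 = 9 days.
- Share of the time from randomisation to 6 weeks post-partum: 9/(11 + 42) = 9/53 = 17%.
- Share of mean antepartum time lost to the lag: 2/11 = 18%.
- Women who deliver before the window opens: 3.6% if delivery time is normal, 0.3% if it is gamma, so about 2 of 64 at most.

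**Effect of unequal windows on the risk ratio**

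With a 3-day prolongation the mean window on pravastatin is 14 − 2 = 12 days. If every woman had the mean window and the control risk were p, the apparent ratio would be [1 − (1 − p)^(12/9)]/p:
- p = 0.10: (1 − 0.869)/0.10 = 1.31
- p = 0.20: (1 − 0.743)/0.20 = 1.29
- p = 0.40: (1 − 0.506)/0.40 = 1.23

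Letting delivery time vary as a gamma distribution (mean 11, SD 5, scaled by 14/11 on pravastatin) gives 1.31, 1.28 and 1.22. The uncorrected chi-squared test at 32 per arm then rejects in 7–12% of trials, against 5–6% with equal windows. On the same model:
- A 5-day prolongation gives ratios of 1.35–1.50.
- A pregnancy 3 days shorter gives 0.68–0.73.
- A true hazard ratio of 0.7 at 20% control risk with 3 days' prolongation appears as 0.94, against 0.73 with equal windows.

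**Ratio of mean time at risk if the window runs to 6 weeks post-partum (3-day prolongation)**
- Hazard unchanged after birth: 56/53 = 1.06.
- No hazard after birth: 14/11 = 1.27.
- Present window, for comparison: 12/9 = 1.33.

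**Sparse cells**

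The probability that exactly one arm of 32 has no events is 2q(1 − q), with q = (1 − p)^32:
- p = 0.05: q = 0.194, probability 0.31
- p = 0.10: q = 0.034, probability 0.07

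The planned risk ratio is then zero or undefined. The expected count per arm falls below 5 when the pooled risk is below 5/32 = 15.6%.

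**The case against.** The punctuation would allow the time limit to attach only to the last item, liver transaminases. The severity outcome applies almost the same phrase to its whole list, so the wider reading is the natural one. If the narrower one is meant, the wording still needs repair.

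A reader might infer more than the documents support:
- **That the plan breaches its intention-to-treat principle.** It does not. Section 9.2 defines that principle as analysis by randomised arm regardless of compliance. A woman delivered before 48 hours can stay in the denominator as a non-event, and eligibility (4.2.1, 4.2.4) already makes such cases uncommon.
- **That this is the main maternal harm outcome, so harms are lost to the trial.** SAEs are a separate secondary outcome, adverse events run to 6 weeks, and section 7.1 names eclampsia, cerebrovascular event and pulmonary oedema among the expected SAEs. The events leave one endpoint, not the trial. SAE reporting is not a full substitute, because a creatinine or proteinuria threshold need not meet the definition of serious.
- **That the 48-hour start should go from the severity outcome too.** No separate argument supports this. A delayed start is defensible: the first dose may be given the evening after randomisation (6.2.2), and women may already meet a criterion at entry.
- **That the bias has a known direction.** Several listed events are also agreed indications for delivery (6.5.1). An event can close its own window, which a constant hazard ignores.

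It also stands that a window ending 6 weeks after birth still depends partly on the length of pregnancy. Its gain is large if risk continues after birth and small if it does not.

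**Conclusion.** The concern holds for the definition of this one secondary endpoint. Section 8.2 and Table 1 disagree on when maternal morbidity counts. Followed as written, 8.2 leaves out post-partum events that are collected, and it ends at a time that treatment may change. The ratio of about 1.2–1.3 illustrates how far the comparison could shift under an assumed 3-day prolongation, equal constant hazards and 10–40% control risk. It is not a forecast, and the arms' windows differ only if the drug alters time to delivery. The trial is not powered for clinical outcomes (2.4.1), so the consequence is for the reading of safety and clinical benefit and for planning the next trial. The primary sFlt-1 result is unaffected. The sparse-data point depends on the event rate, which the plan does not give: it matters at about 5% risk and much less at 10%.

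**What to change.** In section 8.2, reconcile the definition and the collection sentence with Table 1:
- Count new-onset morbidity, meaning a criterion not already met at baseline, in all randomised women from randomisation to 6 weeks post-partum.
- Report antepartum and post-partum events separately, so that any effect of pregnancy length can be seen.
- Keep the present version (after 48 hours, antepartum) as supportive.
- Leave the 24-hour proteinuria component antepartum, because Table 1 schedules no such measurement at or after birth.

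In section 9.2, or in the Statistical Analysis Plan to which it defers detail, specify Fisher's exact or a mid-p test, with score or exact intervals for the risk difference, when any expected count is below 5.

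The cost is wording in the protocol and analysis plan, on data that are largely scheduled already. The drawback is that events before the drug can act add some noise; the supportive version shows how much this matters.

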**Table 1 Secondary outcome measures**

| Assessment or outcome                                             | Prior to randomisation | Repeatedly during pregnancy | At child-birth | Repeatedly until discharge | At 6 weeks post child-birth |
|-------------------------------------------------------------------|------------------------|-----------------------------|----------------|----------------------------|-----------------------------|
| Clinical Measures                                                 |                        |                             |                |                            |                             |
| Blood pressure                                                    | X                      | X                           | X              | X                          | X                           |
| Biochemical Measures                                              |                        |                             |                |                            |                             |
| Protein dipstick                                                  | X                      | (X)                         | (X)            | (X)                        |                             |
| 24hr urine protein                                                | X (if possible)        | (once weekly, if possible)  |                |                            |                             |
| Urinary protein:creatinine ratio                                  | X                      | X                           | X              | X                          | X                           |
| Urea                                                              | X                      | X                           | X              |                            |                             |
| Serum creatinine                                                  | X                      | X                           | X              | X                          | X                           |
| Serum uric acid                                                   | X                      | X                           | X              | X                          |                             |
| Albumin                                                           | X                      | X                           | X              | X                          |                             |
| Liver transaminase                                                | X                      | X                           | X              | X                          | X                           |
| Total cholesterol                                                 | X                      | X                           | X              | X                          |                             |
| C-reactive protein                                                | X                      | X                           | X              | X                          |                             |
| Haematological Measures                                           |                        |                             |                |                            |                             |
| Heamoglobin                                                       | X                      | X                           | X              |                            |                             |
| Platelet count                                                    | X                      | X                           | X              | X                          | X                           |
| WCC                                                               | X                      | X                           | X              |                            |                             |
| Biomarkers                                                        |                        |                             |                |                            |                             |
| Plasma sFlt/ sEng/ PIGF                                           | X                      | X                           | X              | X                          | X                           |
| Anti-hypertensive/ other pre-eclampsia treatment                  | X                      | X                           | X              | X                          |                             |
| Maternal mortality/ morbidity                                     |                        | X                           | X              | X                          | X                           |
| Fetal & Neonatal Measures                                         |                        |                             |                |                            |                             |
| CTG                                                               | X                      | X                           |                |                            |                             |
| Liquor volume                                                     |                        | X                           |                |                            |                             |
| Umbilical artery Doppler                                          | X                      | x                           |                |                            |                             |
| Maternal serum and umbilical cord blood pravastatin concentration |                        |                             | X              |                            |                             |
| Gestational age                                                   |                        |                             | X              |                            |                             |
| Apgar score at 1,5,10 minutes                                     |                        |                             | X              |                            |                             |
| Congenital anomalies                                              |                        |                             | X              |                            | x                           |
| Neonatal mortality/ morbidity                                     |                        |                             | X              | X                          | X                           |
| Length of maternal and perinatal hospital stay and location       |                        |                             |                | X                          |                             |
| Serious adverse events or reactions                               | X                      | X                           | X              | X                          | X                           |

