### **8.3. Format and timing of outcome measures**

All women with early onset pre-eclampsia will be admitted into hospital until child-birth, enabling baseline and follow-up data to be collected directly from hospital notes onto the StAmP data collection forms and the online trial database. The local PI, nominated investigators or research midwives will be responsible for data collection and entry on to the database.

The baseline clinical measurements will be those taken most immediately prior to randomisation and used to diagnose pre-eclampsia and determine the severity of the condition.

All daily biochemical, haematological and clinical measurements, concomitant medications, fetal assessments and indicators of maternal morbidity will be collected on StAmP data collection forms to ensure important events are recorded and to determine which events or reactions should be reported as serious adverse events or suspected unexpected serious adverse reactions.

On the day of birth of the baby, neonatal outcomes will be recorded. Appropriate data collection forms will be completed until discharge.

The final time-point is at 6 weeks post-partum. An out-patient appointment with the investigator and/or local PI and ideally the research midwife will be made as close to this time-point as possible. Post-partum data collection forms will be used to collect secondary outcome measurements from maternal and neonatal notes and any additional information direct from the parents. A final additional blood sample will be required for biomarker assay.

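### Neonatal length of stay has no rule for death, so the arm with more early deaths tends to show the shorter stay; the start of maternal stay should also be put into words

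*Combined protocol and SAP*

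**What the plan says.** Section 8.2 introduces the table with the sentence "The data items collected to identify secondary outcomes are shown in Table 1". One row is "Length of maternal and perinatal hospital stay and location". Its only tick is under the column for repeated recording until discharge, which follows the child-birth column. The row is not among the bulleted outcomes of section 8.2.

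Section 9.2 describes a repeated-measures model for the biomarkers and a Cox model for length of gestation. It then says "All other continuous measures (clinical measures, etc) will be considered in the same manner as above", adjusting for baseline where there is one. On deaths it says "Dichotomous outcomes (mortality, etc) will be presented as risk ratios".

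No section says when either stay starts or ends, which babies are counted, or what happens to a stay that ends in death or is still running at the 6-week final time-point of section 8.3. Section 9.2.1, on missing data, plans multiple imputation as a sensitivity analysis and does not mention death. Section 9.2 leaves further detail to a Statistical Analysis Plan, which is not part of the supplied text.

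**The concern.** Length of stay reads as a burden: shorter is better. That holds only for babies who go home. A baby who dies on day 3 has a stay of 3 days, shorter than almost any survivor's after a very preterm birth. If that value enters the analysis like any other, each early death improves its arm's result.

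The second question in section 2.5 asks about adverse or beneficial effects on mother and baby, and section 2.6 says the clinical outcomes will inform later trials. A neonatal stay result with the wrong sign would carry into that planning. Deaths are a realistic prospect: section 2.4.1 calls the condition life-threatening for the offspring, and Table 1 records neonatal mortality at three time points.

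**Working it through.** The protocol gives no figure for length of stay, so there is none to reproduce. Its only sample size calculation (section 9.1) is for sFlt-1 and is not affected. I take perinatal stay to mean the baby's stay.

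**Inputs**
- From the protocol: up to 64 women (section 9.1), equal allocation (section 5.3), so at most 32 babies per arm; two-sided tests (section 9.2), with 5% taken as the level.
- Assumed, because the protocol gives no values: survivors' mean stay S = 42 to 49 days; a baby who dies does so at day 3; neonatal mortality 5% in one arm and 10% or 15% in the other; survivors alike in both arms.

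**Size of the distortion**

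Mean stay in an arm with mortality p is (1 − p) × S + p × 3.
- S = 42: at 5%, 0.95 × 42 + 0.05 × 3 = 40.05; at 15%, 0.85 × 42 + 0.15 × 3 = 36.15. The arm with three times the deaths is 3.9 days shorter.
- S = 49: 46.70 v 42.10, so 4.6 days shorter.
- In general the gap is (difference in mortality) × (S − 3). At 5% v 10% it is 0.05 × 39 = 1.95 to 0.05 × 46 = 2.3 days.
- With S from 30 to 60 days, the gap is 1.35 to 2.85 days at 5% v 10%, and 2.7 to 5.7 days at 5% v 15%. The direction never changes.

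**Can the sign reverse?**

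Take S = 45 and 15% mortality on placebo: mean 0.85 × 45 + 0.15 × 3 = 38.70. Suppose the drug cuts mortality to 5% and shortens survivors' stay by 3 days: mean 0.95 × 42 + 0.05 × 3 = 40.05. A drug better on both counts shows a stay 1.35 days longer. The sign turns only when survivors' stay falls by about 4.4 days, since (38.70 − 0.15) / 0.95 = 40.58 and 45 − 40.58 = 4.42.

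**Would it reach significance?**

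Assume no variation at all among survivors, which overstates power. S then cancels:

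z = 0.10 / √[(0.05 × 0.95 + 0.15 × 0.85) / 32] = 0.10 / √(0.175 / 32) = 1.35, which is about 27% power.

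At 5% v 10%, z = 0.05 / √(0.1375 / 32) = 0.76, about 12%. Real variation among survivors lowers both. The harm is a misleading point estimate and interval more than a false positive test.

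**The case against.** **Mortality is reported anyway.** Section 9.2 gives it as a risk ratio, and section 7.5 sends all deaths to the DMEC. A careful reader can therefore see the deaths. That does not repair the stay comparison, in which they still count as short stays.

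**No method is named for this row.** True. The default sentence follows both a mixed model and a Cox model, so a comparison of mean days is an inference. But a Cox model needs a death rule too. Counting death as the end of stay makes it a fast discharge; censoring at death treats the baby as still able to go home.

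**The item is minor.** This stands. It is absent from the 8.2 bullets, section 2.4.1 says the trial is not powered for clinical outcomes, and the later Statistical Analysis Plan could settle it.

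**A stronger maternal reading is tempting.** Section 8.3 says "All women with early onset pre-eclampsia will be admitted into hospital until child-birth", and section 8.2 says "length of gestation post randomization will be considered the most important indicator of potential clinical efficacy". A reader might infer that each day of pregnancy gained is scored as a worse maternal stay. Counted from admission or randomisation, it would be. With the protocol's 11±5 days to delivery and an assumed postnatal stay of 4-7 days (SD 2), a 4-day gain lengthens total stay by 4/18 to 4/15, or 22-27%. The SD is √(25 + 4) = 5.39, the standard error 5.39 × √(2/32) = 1.35, and z = 2.97, about 84% power.

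The documents do not support stating this as fact. The row is not ticked for the pregnancy period, and the only other mention of maternal stay, in the SAE definition of section 7.1, is post-natal. On that reading a day gained adds nothing. What remains is that the start point is not put into words. Nor does any section call a longer maternal stay a harm.

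**Conclusion.** The neonatal point holds. The plan lists length of perinatal stay under the secondary outcome measures and provides no rule for death, so early deaths favour the arm in which they occur. The distortion is about 4 to 5 days at 5% v 15% mortality and about 2 days at 5% v 10%. The direction follows from the arithmetic whenever deaths come earlier than survivors' discharge; the size rests wholly on assumed mortality, survivor stay and day of death. A significant false result is unlikely at this sample size.

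The maternal point is a request for one clarifying sentence; it does not show that the outcome runs against length of gestation. Overall this is a small change worth making before the analysis plan is final.

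**What to change.** In Table 1 and section 9.2:

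1. Replace neonatal length of stay with time from birth to discharge home alive. Treat death before discharge as a competing event and report cumulative incidence by arm; or use a rank comparison with death as the worst rank. Exempt this outcome from the default rule for continuous measures.
2. Censor babies still in hospital at the 6-week final time-point. In a rank comparison, place them below those discharged and above deaths.
3. State that stillbirths count as never discharged alive, or that they are excluded and reported alongside.
4. State that maternal stay runs from delivery to discharge. Antenatal days are already covered by length of gestation.

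The cost is wording; sample size and treatment do not change. The result becomes a cumulative incidence or rank comparison in place of a difference in mean days. If stays are as long as assumed here, many babies will be censored at 6 weeks and the result describes discharge by that time only. The protocol does not list the dates of birth, discharge and death as collected items. Forms run until discharge (section 8.3) and deaths go on the SAE form (section 7.5), so they should be available, but check this against the forms.
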